## Abstract

**Background:**

Migraine is a complex, chronic, and debilitating multifactorial disorder characterized by recurrent episodes of headache and related symptoms. It typically begins in early ages and is more prevalent in women than in men. Recently, the gut–brain axis has emerged as a new candidate that may be linked to neurological diseases. We hypothesize that selective modulation of the intestinal microbiota, oxidative stress, and inflammation through inulin supplementation may improve clinical outcomes in these patients. Therefore, this study aims to examine the effects of high-performance inulin supplementation on clinical symptoms, mental health, quality of life (QOL), intestinal permeability, and inflammatory and oxidative stress factors in women with migraine.

**Methods:**

This is a randomized, double-blind, placebo-controlled clinical trial involving 80 women with migraine who meet the inclusion criteria (aged between 20 and 50 years with a diagnosis of migraine by a neurologist based on the ICDH-3). Participants will be assigned to receive a daily dose of 10 g of inulin for 12 weeks (intervention group, *n* = 40) or 10 g of maltodextrin as a placebo for the same duration (control group, *n* = 40). The primary outcome will measure the variations in the frequency of headache experienced by the patients. Secondary outcomes will encompass serum levels of zonulin, high-sensitive C-reactive protein, total antioxidant capacity, total oxidant status, nitric oxide, mental status, QOL, duration, and severity of migraine attacks.

**Discussion:**

This clinical trial aims to evaluate the effect of inulin supplementation on inflammatory status, oxidative stress, intestinal permeability, clinical symptoms, mental health, and QOL in women with migraine. The findings of this trial could contribute to the identification of mechanistic action and evidence-based clinical guidelines that address gut microbiota manipulation to maximize health benefits in the management of clinical outcomes in migraine patients.

**Trial registration:**

Iranian Registry of Clinical Trials (www.irct.ir) (ID: IRCT20121216011763N58). Registration date: 23 April 2023.

**Trial status:**

The protocol is version 3.0, September 17, 2023. Recruitment began August 21, 2023, and is anticipated to be completed by March 22, 2024.

**Supplementary Information:**

The online version contains supplementary material available at 10.1186/s13063-023-07765-4.

## Introduction

### Background and rationale {6a}

Migraine is a complex, chronic, and debilitating multifactorial disorder, characterized by recurrent episodes of headache and related symptoms, such as photophobia, phonophobia, nausea, vomiting, vertigo, and cognitive dysfunction, which lasts for 4–72 h [1, 2]. The prevalence of migraine is estimated to be around 12% of the general population, with the highest occurrence observed among individuals aged 18 to 44 years. Women are more susceptible to migraines compared to men, with prevalence estimates ranging from 5 to 25% worldwide [3, 4]. Although the prevalence of migraine is generally lower in Asian populations compared to Western countries [5], it is noteworthy that the prevalence of this disease in Iran is approximately 15.1%, which is higher than global comparators [6].

The exact pathogenesis of migraine remains incompletely understood; however, there is a general consensus that it results from a complex interplay of vascular and neural events [7]. Several mechanisms have been proposed to explain the development of migraines, including neuro-inflammation, vascular dysfunction, and the gut–brain axis [7–10]. In recent years, there has been growing interest in the role of microbiota and gut health in the prevention and development of neurological disorders [11, 12]. The bidirectional interaction between the enteric and central nervous systems, known as the gut–brain axis, has been suggested to play a role in the association between the brain, gut microbiota, and cognitive function [13]. Furthermore, the composition of the gut microbiota plays a significant role in the gut–brain axis through direct connections with stimulating end terminals of the vagus nerve and indirect signaling involving inflammatory molecules, microbiota-derived neurotransmitters, and hormones [14]. Also in this case, the mechanism is bidirectional as the central nervous system (CNS) can modulate gut microbiota through the parasympathetic and sympathetic systems and by releasing neuroendocrine peptides [15]. Alterations in the profile of the intestinal microbiota may occur due to the influence of both physical and psychological stress factors. These stressors may result in dysbiosis, a condition where the composition of the gut microbiota undergoes alterations [16, 17].

Recent evidence suggests that oxidative stress and inflammation contribute significantly to the pathogenesis of migraines by triggering the abnormal activation of nociceptive sensory neurons [18, 19]. In this regard, migraine attacks may be neuro-protective responses to elevated oxidative stress and inflammation in the brain [20]. Moreover, it is important to note that a dysbiosis of the gastrointestinal tract microbiota and an increase in gut permeability could potentially trigger the activation of the hypothalamic–pituitary–adrenal axis. This activation is typically mediated by the release of pro-inflammatory cytokines such as (IL)-1β, high-sensitivity CRP (Hs-CRP), IL-6, tumor necrosis factor-alpha (TNF-α), and IL-8 [21, 22]. It is noteworthy that synthetic antioxidants such as 5-(5-substituted-1,3,4-oxadiazol-2-yl) benzene-1,2,3-triols and 5-substituted-1,3,4-thiadiazole-2-thiols have displayed very high and significant antioxidant activities in several studies [23, 24]. These findings raise the prospect of using oxidative stress modulator-synthetic antioxidants as therapeutic interventions for migraine patients.

Dietary components such as fiber, prebiotics, and probiotics have the potential to significantly influence the mechanisms by which the gut microbiota regulates immune function and gastrointestinal health [25]. Short-chain fatty acids (SCFAs), including butyrate, acetoacetate, and propionate, play a crucial role in maintaining gut barrier integrity [26]. In addition to their role in maintaining homeostasis and mitigating inflammation within the gastrointestinal tract, SCFAs are also known for their neuroprotective properties and their ability to modulate immune responses [26]. Interestingly, the supplementation of prebiotics, specifically fermentable fibers, to a high-fat diet has been reported to counteract the reduced levels of butyrate-producing bacteria and Bifidobacteria [27, 28].

The potential for supplementation with prebiotics and probiotics to modulate the frequency and severity of migraine attacks is an area of ongoing research. The exact mechanisms through which this modulation occurs remain somewhat elusive, but several hypotheses have been proposed. One such hypothesis suggests that prebiotics and probiotics may enhance the production of SCFAs in the gut. Another theory posits that these supplements could strengthen the integrity of the intestinal epithelium. Furthermore, these supplements may exert an anti-inflammatory effect by suppressing the nuclear factor kappa-B (NF-κB) pathway, thereby reducing levels of pro-inflammatory cytokines [29, 30]. However, these mechanisms necessitate further investigation to fully comprehend their implications in the context of migraine management. In 2019, a randomized clinical trial evaluated the effect of daily administration of a complex 14-strain probiotic mixture versus a placebo over 8 weeks in patients with chronic migraines and 10 weeks in those with episodic migraines. The administration of the probiotic mixture resulted in significant improvements in the frequency and severity of migraines, as well as a reduction in the usage of abortive medications within the studied population. Notably, these improvements were observed despite the absence of significant alterations in the serum levels of inflammatory biomarkers [29]. In another study conducted in Iran in 2021, a 12-week intervention with synbiotic led to a significant reduction in the average frequency of migraine attacks, the number of painkillers used, and gastrointestinal problems. Moreover, the synbiotic group exhibited lower levels of zonulin and Hs-CRP, which are markers of intestinal permeability and inflammation, respectively. However, the authors did not observe any beneficial effect of synbiotic supplementation on migraine severity and duration [10]. In a subsequent study, the administration of a probiotic mixture composed of seven bacterial strains resulted in approximately 25% reduction in the frequency of migraine attacks [31].

As previously discussed, functional foods such as probiotics and synbiotics have been shown to influence migraine symptoms in recent studies [10, 29, 32]. However, the role of prebiotics in this condition is still not well understood. Inulin-type fructans are a group of functional foods that can enhance the properties of beneficial intestinal bacteria. High-performance inulin (HP inulin) is a prebiotic with long-chain, high-molecular-weight mixes of inulin-type fructans. Inulin supplementation has been demonstrated to elicit several health benefits, including immune system regulation [33], anti-inflammatory effects [34], anti-depressant effects [35], and antioxidant effects [36]. Previous studies have indicated that prebiotics can induce specific changes in the activity and/or composition of the gut microbiota, particularly bifidogenic effects, which can have a beneficial impact on inflammation by balancing endothelial function and gut permeability [37, 38]. Therefore, prebiotic supplementation could be a beneficial strategy for reducing the frequency and severity of migraine attacks and improving the quality of life (QOL) for these patients. To the best of our knowledge, no published clinical trials have yet evaluated the impact of inulin on migraine patients. Consequently, this study is designed to investigate the potential effects of HP inulin supplementation on various aspects, including clinical symptoms, mental health, QOL, intestinal permeability, as well as inflammatory and oxidative stress markers in women suffering from migraines.

### Objectives {7}

The current study aims to evaluate the impact of HP inulin supplementation on inflammatory status, oxidative stress, intestinal permeability, clinical symptoms, mental health, and QOL in women with migraines. If this study confirms our hypothesis, inulin supplementation may be used to enhance the effects of existing migraine treatments.

### Trial design {8}

A randomized, parallel, two-arm, double-blind, and placebo-controlled superiority clinical trial will be conducted.

## Methods: participants, interventions, and outcomes

### Study setting {9}

This clinical trial will be carried out at the neurology clinic affiliated with Isfahan University of Medical Sciences in Isfahan, Iran.

### Eligibility criteria {10}

#### Inclusion criteria

The inclusion criteria will consist of patients who meet the following conditions:Aged between 20 and 50 years with a diagnosis of migraines by a neurologist ([name]), based on the International Classification of Headache Disorder-3 (ICDH-3)Residents of Isfahan city who are willing to participate in the studyFill out a written informed consent form prior to participation in this trial

#### Exclusion criteria

The exclusion criteria will consist of patients who meet the following conditions:Subjects who have/had other types of headaches such as tension-type headache or medication overuse headachePregnant or breastfeeding subjectsSubjects on a special diet or consuming nutritional supplements (probiotics, prebiotics, and dietary fiber supplements)Subjects who have/had gastrointestinal disorders like Crohn’s disease and ulcerative colitis, as well as other neurological disordersSubjects who have/had use of antibiotics and anti-acids drugs in three months pastSubjects who are unwilling to continue with the study

### Reason for eliminating the data

Consumption of less than 80% of inulin supplements by the patient.

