#### Strategies to improve adherence to interventions {11c}

Patients will be provided with inulin and placebo packs at weeks 1, 4, and 8. At the baseline, each phone call, and intermediate visits, all patients will receive instructions on how to use their supplements. They will be requested to return the packs with any remaining contents at the end of each 4-week period, and any side effects experienced will be recorded. Additionally, patients will be asked to complete a daily calendar immediately after consuming their assigned treatments. Adherence to intervention refers to the extent to which trial participants’ behavior aligns with their assigned intervention. Adherence to the assigned treatments will be assessed through the use of a daily calendar during each phone call and by counting the returned packs at the end of the trial. Compliance will be calculated using the following formula: Compliance rate = (packs taken / packs prescribed) × 100. A compliance rate below 80% will be classified as poor compliance.

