### Sample size {14}

The sample size for the present study was calculated based on means and standard deviations for the frequency of attacks, as the main outcome of the study of Ghavami et al. [41], by considering a 95% confidence interval and 80% power (*α* = 0.05 and *β* = 0.2). Frequency of attacks was also considered a main outcome, and based on a previous study, the sample size was calculated as 40 patients for each group. All patients who meet the inclusion criteria and are willing to participate in the trial will be included until the estimated sample size is completed.

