### Statistical methods

#### Statistical methods for primary and secondary outcomes {20a}

Statistical analyses will be conducted using SPSS (version 21.0) software. A *P*-value < 0.05 will be considered statistically significant. The one-sample Kolmogorov–Smirnov test will be used to evaluate the normality of the distribution of data. Regarding missing values, the data analysis will be subjected to intention-to-treat (ITT) analysis. We will employ the multiple imputation approach to perform ITT. In order to compare the baseline value of qualitative and quantitative variables, the chi-square test and *t*-test will be used. Categorical variables will be expressed as number and percentage, while quantitative data will be presented as mean ± standard deviation. Between-group differences will be evaluated using a Mann–Whitney *U* test and independent *t*-test. Differences within the group will also be assessed with a Wilcoxon rank-sum test and paired *t*-test. To control for confounders, an analysis of covariance (ANCOVA) will be carried out.

The primary results of this study include the evaluation of clinical symptoms of patients, such as headache frequency, duration, and severity. The secondary results encompass the evaluation of the serum levels of zonulin, Hs-CRP, TAC, TOS, NO, mental health status, and QOL by questionnaire.

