#### Interim analyses {21b}

The recruitment of participants for the trial and their engagement in the intervention will be diligently monitored. The continuation criteria will be reviewed periodically throughout the course of the study. An intention-to-treat analysis will be conducted for participants who drop out during treatment sessions or follow-up assessments. It is important to note that participants who drop out will not be excluded from the data analysis. The study will be stopped upon the completion of participant enrollment, provided that no serious adverse events transpire during the course of the study. In the event that adverse events do occur, the study will be promptly discontinued. Adverse events encompass occurrences such as death, disability, and severe allergic reactions that have a substantial impact on the patient’s health. This trial does not include any planned interim analyses.

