#### Methods in analysis to handle protocol non-adherence and any statistical methods to handle missing data {20c}

The analysis will follow an ITT approach, which will include the data from the excluded patients in the results. The reason for each patient’s withdrawal, especially the occurrence of any side effects, will be explained in detail. Missing data will be addressed by multiple imputations.

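### The rule that eliminates data for consumption below 80% conflicts with the intention-to-treat commitments, and nothing limits it to a per-protocol set

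*Protocol article*

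**What the plan says.** The section headed "Reason for eliminating the data" follows the eligibility criteria and contains one line: "Consumption of less than 80% of inulin supplements by the patient". It concerns data, not treatment, and mentions no per-protocol or sensitivity analysis.

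Section {11c} uses the same threshold differently. There, compliance is packs taken divided by packs prescribed, times 100, and "A compliance rate below 80% will be classified as poor compliance". This is a label with no consequence for the data, and it covers everyone: "Adherence to the assigned treatments will be assessed through the use of a daily calendar".

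Three statistical sections describe a different analysis population:
- {20a}: "the data analysis will be subjected to intention-to-treat (ITT) analysis", carried out with multiple imputation.
- {20c}, on non-adherence and missing data: "The analysis will follow an ITT approach, which will include the data from the excluded patients in the results".
- {21b}: "participants who drop out will not be excluded from the data analysis".

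**The concern.** The two sets of statements give different answers for the same patient. Someone who takes 60% of her packs and has a recorded end-of-trial headache frequency is eliminated under one section and analysed under another. With no stated order of precedence, the primary analysis population could be chosen after the results are seen.

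Adherence is measured after randomisation and can depend on tolerability and perceived benefit. Patients above the threshold are therefore not a randomised subset, and comparing them across arms no longer has the protection of the allocation. Multiple imputation does not repair this. Deleting observed outcomes of poor adherers and imputing them would replace real values with values modelled largely from adherers.

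**Working it through.** **Where the conflict bites.** One pack a day for 12 weeks is 12 × 7 = 84 packs, and 0.80 × 84 = 67.2. A patient who takes 67 packs or fewer (67/84 = 79.8%) falls below the threshold.

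| Section | Patient below 80% with an observed outcome |
|---|---|
| Section on eliminating data | Data removed |
| {11c} | Labelled poorly compliant, nothing removed |
| {20a} | Analysed (intention-to-treat) |
| {20c} | Analysed, even if excluded |
| {21b} | Does not address adherence, but keeps dropouts |

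The first row cannot be reconciled with {20a} and {20c} unless it is either without effect or confined to a secondary analysis. The article says neither.

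**Possible size of the bias.** The documents give no non-adherence rate and no outcome difference between adherers and others, so these are assumptions. Let f be the share of an arm removed and k the amount, in SD, by which those removed do worse than those kept. The mean of the kept patients then looks better than the mean of the whole arm by f × k.

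Removal from the inulin arm only, with no true effect:
- bias = f × k
- SE = √(1/40 + 1/n₁), with n₁ = 40(1 − f) and SD = 1
- type I error = P(Z > 1.96 − bias/SE) + P(Z < −1.96 − bias/SE), a normal approximation

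| f | n₁ | k | bias (SD) | SE | type I error |
|---|---|---|---|---|---|
| 0.15 | 34 | 0.5 | 0.075 | 0.233 | 6.2% |
| 0.15 | 34 | 1.0 | 0.15 | 0.233 | 9.9% |
| 0.20 | 32 | 0.5 | 0.10 | 0.237 | 7.1% |
| 0.20 | 32 | 1.0 | 0.20 | 0.237 | 13.5% |

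Removal from both arms: bias = f₁k₁ − f₀k₀ (1 = inulin, 0 = placebo). If the shares and gaps are alike, this is close to zero under the null. The table then does not apply.

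**Precision.** With equal removal in both arms, the standard error grows by √(40/n): √(40/34) = 1.08 at 15% and √(40/32) = 1.12 at 20%.

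Power needs one more assumption. Section {14} states only that "the sample size was calculated as 40 patients for each group" at 80% power and gives no mean difference or SD, so its figure cannot be reproduced. If 40 analysed per arm gives exactly 80% (two-sided 5%), the implied standardised difference is √(2/40) × (1.960 + 0.842) = 0.626. At that value:

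| Analysed (inulin vs placebo) | Power |
|---|---|
| 34 vs 40 (inulin only, 15%) | 76.6% |
| 32 vs 40 (inulin only, 20%) | 75.2% |
| 34 vs 34 (both arms, 15%) | 73.3% |
| 32 vs 32 (both arms, 20%) | 70.7% |

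The two scenarios should not be mixed: the inflated type I error goes with the one-arm rows, and the larger power loss with the two-arm rows.

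**The case against.** The best defence is that {20c} already answers the question. It is the section on non-adherence and keeps the data of excluded patients, and {20a} and {21b} point the same way. On that reading, the section on eliminating data merely defines who counts as excluded, and the planned primary analysis is sound. This has force and makes a biased primary analysis less likely. But the elimination rule would then have no effect, contrary to its heading, and the article states no precedence. The texts still have to be reconciled.

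A reader might infer more than the documents support:

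- **That the rule is meant for the inulin arm only.** Controls receive maltodextrin, so the literal wording does not cover them. But {11c} applies the same threshold to both arms, and {18b} appeals to the benefits of inulin to retain all participants. Under {16b} and {17b} the A/B labels stay masked until the end, so an inulin-only rule could not ordinarily be applied earlier. Loose wording is a fair explanation.
- **That the bias must favour inulin.** This requires poor adherers to do worse. That is plausible if intolerance or lack of benefit drives non-adherence, but patients who feel better may also stop taking packs. The documents give no sign or size.
- **That the exclusion criterion on unwillingness to continue removes randomised patients.** Table 1 places eligibility testing and consent at week −1 and allocation at week 0, so the criterion can be read as a screening one. Section {21b} keeps dropouts in any case.
- **That the trial is too small because 40 per arm leaves no room for loss.** Section {14} does not say whether 40 includes an allowance for attrition, so this cannot be established.

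**Conclusion.** The contradiction is established from the text alone: one section eliminates data below 80% consumption, while {20a} and {20c} commit to analysing those patients. It concerns who enters the primary comparison, so it should be settled before the randomisation codes are unlocked. This does not depend on an unseen analysis plan, because the article itself states both rules.

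The size is illustrative only. If the rule were followed in the inulin arm alone, the spurious difference would be 0.075-0.20 SD and the type I error about 6-13.5%, given the assumed 15-20% removed and a 0.5-1.0 SD worse outcome. If it were followed in both arms with similar shares and gaps, bias under the null would be small and the main cost would be a standard error about 8-12% larger. Neither the one-arm intent nor a bias towards inulin is shown by the documents.

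**What to change.** Delete the section on eliminating data as a rule that removes data. State once, in {20a} or {20c}, that all 80 randomised patients are analysed in the group to which they were assigned, that observed outcomes are used whatever the compliance, and that multiple imputation is used only for values truly missing.

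If an adherence-based analysis is wanted, define it as a secondary per-protocol analysis. Use the {11c} definition (packs taken over packs prescribed, threshold 80%), refer to the assigned product instead of inulin, and apply it identically in both arms.

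The cost is wording only. The headline effect may come out slightly smaller than in an adherers-only analysis. No stated sample size or other figure changes.
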